##### **13.1.3. Efficacy outcomes**

- Efficacy outcomes will be analyzed for both the per-protocol (PP) and ITT populations. In case of discrepancies between the efficacy outcomes of PP and ITT populations, both set of results will be presented and compared, with the PP population considered the main

Version 2.6

analysis and the ITT population as supplementary analysis.

- The ITT population consists of participants who received at least one dose of the clinical trial drugs and underwent efficacy evaluation more than once during the treatment period. In cases of missing values due to dropouts or discontinuation before the clinical trial ends, missing data from dropout participants will be imputed using the last observation carried forward analysis.
- The PP population is a subset of the ITT population. It includes participants who consumed >70% of the prescribed doses of clinical study drugs and completed follow-up visits and corresponding outcome measurements (weeks 4, 8, and 12) during the 12-weeks treatment periods. Participants falling under a 'significant violation of clinical trial plan' will be excluded from the PP population.

### **13.2. Demographic data**

- Data will be presented as the mean  $\pm$  SD for continuous data or frequencies for categorical data.
- To confirm the validity of the random allocation, demographic and baseline values between the experimental and control groups will be compared and evaluated. We will use the independent t-test or Mann-Whitney U test for continuous outcome measures and the chi-square test, Fisher's exact test, or Cochran-Mantel-Haenszel Method for categorical outcome measures.
- 

### **13.3. Efficacy assessment**

#### **13.3.1. Primary outcome efficacy assessment**

##### **13.3.1.1. Evaluation item**

Version 2.6

- Unstimulated Salivary Flow Rate (SFR) after 12 weeks of treatment

#### **13.3.1.2. Statistical methods**

- A 95% confidence interval (95% CI) will be used to analyze primary outcomes.
- We will calculate the 95% CI of the mean difference in the unstimulated SFR between the two groups after 12 weeks of medication. If the lower end of the 95% CI of the mean difference is greater than the non-inferiority limit ( $-0.21$ ), it will be concluded that the experimental group is not inferior to the control group.
- For further analysis, if the SFR between the two groups satisfy the normality test, a t-test will be performed to compare the two groups in terms of the primary outcomes; otherwise, the Mann-Whitney U test will be performed. If there is a significant difference in baseline values between the two groups, repeated-measures analysis of covariance (ANCOVA) will be performed.

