#### 8.4. Basis for sample size calculation

- The aim of this prospective, randomized, open-label, parallel-group, multi-center, and controlled trial is to ascertain whether combined administration of BIT herbal medicine and low-dose pilocarpine can demonstrate both non-inferior efficacy and fewer side effects in patients with frequent intractable xerostomia (patients who underwent radiation therapy to the head and neck or with Sjogren's syndrome) than the administration of only high-dose pilocarpine.
- The assumptions for calculating the valid sample size are as follows.
  - ① One-sided Z test (Non-inferiority test)
  - ② Level of significance ( $\alpha$ ) = 0.05 (Considering this is an intervention study)
  - ③ Type 2 error ( $\beta$ ) = 0.1 (Power of the test = 90%)
  - ④ Experimental group: Control group = 1 : 1 ( $\lambda=1$ )
  - ⑤ Primary outcome: unstimulated salivary flow rate (SFR) after 12 weeks of treatment
- $\sigma = 0.35$  / d (non-inferiority limit) = 0.21

In the previous study, the mean  $\pm$  standard deviation (SD) of unstimulated SFR for 5 mg pilocarpine therapy vs placebo group after 12 weeks of medication, respectively, were  $0.38 \pm 0.48$  vs  $0.17 \pm 0.13$  mL/min ( $p < 0.001$ ). Based on these results, the SD was calculated to be 0.35.

In consideration of the exploratory aspects of the clinical trial, the point estimation ( $\mu_{CIH}$  -

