## Version 2.6

$\mu_{pH}$ ;  $0.38 - 0.17 = 0.21$ ) after 12 weeks of administration of 5 mg pilocarpine and placebo was set as the non-inferiority limit.

- Reference: Vivino FB, et al. Pilocarpine tablets for the treatment of dry mouth and dry eye symptoms in patients with Sjögren syndrome: a randomized, placebo-controlled, fixed-dose, multicenter trial. P92-01 Study Group. Arch Intern Med. 1999. PMID: 9927101 Clinical Trial.
- The H01 and H11 of this clinical trial are as follows.

H01:  $\mu_c - \mu_t > 0.21$

H11:  $\mu_c - \mu_t \leq 0.21$

$\mu_c$  = SFR after 12 weeks of administration of only pilocarpine one tablet

$\mu_t$  = SFR after 12 weeks of combined administration of Baekhogainsam-tang herbal medicine and low-dose pilocarpine

$$n_c = \frac{(1 + \lambda) \sigma^2 (Z_{\alpha} + Z_{\beta})^2}{\lambda (|\mu_c - \mu_t| - d)^2}$$

$N_c = N_t = 48$

- Assuming a 20% dropout rate, we calculated the sample size as 120 participants (60 in each group).

|                                     | Control | Experimental | Total |
|-------------------------------------|---------|--------------|-------|
| Resultant sample size               | 48      | 48           | 96    |
| Sample size considering 20% dropout | 60      | 60           | 120   |

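### The trial is sized at one-sided alpha 0.05 but judged on a 95% CI (one-sided 0.025), so the stated 90% power is about 84% at the planned 48 per arm

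*Protocol*

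**What the plan says.** Section 8.4 of the Protocol lists the design assumptions:

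- the test: "One-sided Z test (Non-inferiority test");
- the significance level: "0.05 (Considering this is an intervention study");
- the type 2 error: "0.1 (Power of the test = 90"%);
- the allocation: "Experimental group: Control group = 1 : 1";
- the spread: "Based on these results, the SD was calculated to be 0.35" (mL/min);
- the margin: "d (non-inferiority limit) = 0.21" (mL/min).

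The result is 48 per arm. The protocol then allows for losses: "Assuming a 20% dropout rate, we calculated the sample size as 120 participants (60 in each group"). The sample-size part of the protocol summary repeats these assumptions.

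Section 13.3.1.2 gives the decision rule for the primary outcome, unstimulated salivary flow rate at 12 weeks. "If the lower end of the 95% CI of the mean difference is greater than the non-inferiority limit", given there as -0.21, the experimental arm is declared not inferior. The statistical methods part of the summary has the same rule. Neither place says whether the interval is one-sided or two-sided, and neither refers back to the alpha in section 8.4.

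**The concern.** A 95% CI with no qualifier is normally read as two-sided. Requiring its lower end to clear the margin is then a one-sided test at 0.025, half the level used for sizing. On that reading, the 90% power in section 8.4 belongs to a test the protocol does not plan to run.

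Two things are at stake. The first is the power statement, because the risk of failing to show a non-inferiority that truly exists would be larger than the 10% the protocol accepts. The second is the success criterion, because some results would pass at the level in section 8.4 and fail under section 13.3.1.2. In an open-label trial, an ambiguity of this kind in the primary decision rule should be closed before the data are analysed.

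**Working it through.** **Inputs.** SD σ = 0.35, margin d = 0.21, 1:1 allocation, power 90% and 48 evaluable per arm, all from section 8.4. The true difference is not stated. It is taken as 0, because the section 8.4 formula returns 48 only at that value. Normal quantiles: 1.645 (one-sided 0.05), 1.960 (one-sided 0.025), 1.2816 (90% power).

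**Step 1: reproduce the plan's figure.** With λ = 1 and a true difference of 0, the section 8.4 formula is

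n = 2σ²(z_α + z_β)² / d²

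n = 2 × 0.35² × (1.645 + 1.2816)² / 0.21² = 47.6, rounded up to 48 per arm.

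Dropout: 48 / 0.8 = 60 per arm, 120 in total. Both figures agree with the protocol, which confirms that the sizing used one-sided 0.05. (The summary prints the formula without the square on the z-sum, which would give about 16. The version in section 8.4 has the square and is the one that yields 48.)

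**Step 2: power with 48 per arm.**

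SE = 0.35 × √(2/48) = 0.0714

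d / SE = 0.21 / 0.0714 = 2.939

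| Level | Calculation | Power |
|---|---|---|
| One-sided 0.05 (section 8.4) | Φ(2.939 − 1.645) | 90.2% |
| One-sided 0.025 (lower end of a two-sided 95% CI) | Φ(2.939 − 1.960) | 83.6% |

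Using the noncentral t distribution, the second figure is 82.9%. Using the unrounded SD, √((0.48² + 0.13²)/2) = 0.3516, it is 83.3% by the normal calculation.

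**Step 3: sample size for 90% power under the stated rule.**

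n = 2 × 0.35² × (1.960 + 1.2816)² / 0.21² = 58.4, rounded up to 59 evaluable per arm.

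After 20% dropout: 59 / 0.8 = 73.75, so 74 per arm and 148 in total.

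**Step 4: where the two rules disagree.** With SE 0.0714, the observed difference (experimental minus control) must exceed:

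- at one-sided 0.05: −0.21 + 1.645 × 0.0714 = about −0.092;
- at one-sided 0.025: −0.21 + 1.960 × 0.0714 = about −0.070.

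An observed difference between these values passes at one section's level and fails at the other's. If the true difference is 0, the chance of landing there is 90.2% − 83.6% = 6.6%, which is the lost power.

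**The case against.** There are three serious points on the other side.

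*The interval may be meant as one-sided.* Section 13.3.1.2 never says two-sided and uses only the lower end. Read as a one-sided 95% bound, it would match section 8.4 and the power would be 90.2%. This is possible, but it is not the ordinary meaning of a 95% CI, and the text does not say it. If it was intended, section 13.3.1.2 still needs correcting.

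*More than 48 per arm may be analysed.* Section 13.1.3 analyses efficacy in both the per-protocol and ITT sets, and the ITT set carries the last observation forward. If all 60 per arm contributed with the SD unchanged, power at one-sided 0.025 would be 90.8%. The figure is right, but the protocol ties its power to 48, plans for 20% dropout, and lets the per-protocol set lead when the two sets disagree. That set also loses participants for poor compliance, missed visits and major violations, so it could fall below 48. What stands is that 84% is conditional on 48 evaluable per arm.

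*The mismatch is conservative.* The stated rule is stricter than the design level, so it adds no risk of a false non-inferiority claim, and the calculation in section 8.4 is correct for the level it names. Both statements are true. The defect is a conflict between two sections, and its cost is lost power and an unclear criterion.

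**Conclusion.** The concern holds. Section 8.4 and the primary decision rule in section 13.3.1.2 use different error levels, and the 90% power does not describe the rule as written. Under that rule, power is about 84% (83.6% normal, 82.9% t), so the risk of missing true non-inferiority is about 16% instead of 10%. This rests on 48 evaluable per arm, SD 0.35, margin 0.21, a true difference of 0 and the ordinary two-sided reading of the 95% CI. Type I error is not affected. Because the conflict concerns the only success criterion for the primary outcome, it should be resolved before the analysis.

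**What to change.** Use one level throughout.

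- **Preferred:** keep the 95% CI as the decision rule and call it two-sided in section 13.3.1.2 and in the summary. In section 8.4 and the summary, restate alpha as one-sided 0.025 and power as about 84% for 48 evaluable per arm, and state the assumed true difference of 0. The cost is wording and a less favourable stated power. Sample size and analysis do not change.
- **If one-sided 0.05 is really intended:** replace the 95% CI in section 13.3.1.2 and the summary with a two-sided 90% CI, or equivalently a one-sided 95% lower bound. Section 8.4 then stands with 90.2% power. This also costs only wording, but the success rule becomes less strict than the one now written, so the choice must be made and documented before results are seen.

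Keeping both the two-sided 95% CI and 90% power would need 59 evaluable per arm. With 20% dropout that is 148 enrolled, 28 more than planned. The correction does not require this, provided the lower power is stated openly.

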#### 9.5. Random allocation

#### 9.6. Methods of registration and randomization

- An independent statistician, blinded to the study design and purpose, will perform the random allocation of a total of 120 patients to the experimental group or the control group in a 1:1 ratio using a stratified block randomization method (a block size of 4).
- Random numbers will be generated by a computerized random-number generator using the block-randomization method of SAS version 9.1.3 (SAS Institute Inc., NC, Cary, USA) for sequence generation.

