### **13.3.2. Secondary outcomes efficacy assessment**

#### **13.3.2.1. Evaluation items**

- Stimulated SFR after 12 weeks of medication
- Differences and mean percentage changes in unstimulated and stimulated SFR from baseline (week 0) to the end of the trial (week 12)
- Differences and mean percentage change in the visual analogue scale (VAS) and 14-item Oral Health Impact Profile (OHIP-14), and from baseline (week 0) to the end of the trial (week 12).
- Differences and mean percentage changes in the uptake ratio (UR), maximum accumulation (MA), and maximum secretion (MS) on salivary scintigraphy from baseline (week 0) to the end of the trial (week 12).

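### The -0.21 decision rests on an unadjusted week-12 difference, and baseline SFR is used only after a significant baseline test, through an ANCOVA whose role is not defined

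*Protocol*

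**What the plan says.** - **Endpoint.** Protocol 13.3.1.1 names "Unstimulated Salivary Flow Rate (SFR) after 12 weeks of treatment", a final value. Change from baseline appears only among the secondary outcomes.
- **Decision rule.** 13.3.1.2 takes the 95% confidence interval of the between-arm mean difference at week 12 and concludes non-inferiority if its lower end lies above -0.21. No covariate is named.
- **Follow-on tests.** As further analysis, the same section plans a t-test if a normality test is passed; "otherwise, the Mann-Whitney U test will be performed".
- **Baseline.** The section ends: "If there is a significant difference in baseline values between the two groups, repeated-measures analysis of covariance (ANCOVA) will be performed". The protocol summary repeats this wording. Section 13.2 provides for significance tests of baseline values.
- **Data available.** Under 10.2.1 the screening SFR serves as the week-0 value, so every randomised patient should have one. Under 8.1 it is at most 0.25 mL/min, and at most 0.1 for those entering with Sjogren's syndrome.
- **Randomisation.** 9.6 allocates patients "using a stratified block randomization method (a block size of 4"), without naming the strata.
- **Secondary outcomes.** 13.3.2.1 lists "Differences and mean percentage changes in unstimulated and stimulated SFR from baseline" to week 12.

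**The concern.** After valid randomisation, any baseline imbalance is due to chance, so a significance test is a poor guide to whether to adjust. The reason to adjust is that baseline predicts outcome. That gain is present whether or not the arms happen to differ. A rule that adjusts only after a positive test gives the gain up in nearly every trial.

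The rule is also incomplete. It does not say:

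- which baseline values trigger the ANCOVA;
- whether the ANCOVA replaces the confidence interval or accompanies it;
- whether its estimate is compared with -0.21;
- whether a repeated-measures model over weeks 4, 8 and 12 is to yield the week-12 difference or an average over visits.

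If the trigger fires, an open-label trial would hold an unadjusted and an adjusted result with no stated rule for which one carries the conclusion.

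Mean percentage change in SFR raises a smaller, related problem. Eligibility sets a ceiling on SFR but no floor, so the divisor can be zero or close to it.

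**Working it through.** **1. The plan's own figure.** Inputs from 8.4: "One-sided Z test (Non-inferiority test"), alpha 0.05, power 90%, sigma 0.35, margin d 0.21, 1:1 allocation. The true difference is not stated; 0 is taken because it reproduces the result.

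n = 2 × 0.35² × (1.645 + 1.282)² / 0.21² = 47.6, so 48 per arm; 48 / (1 - 0.20) = 60. Both match the protocol.

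**2. Power of the unadjusted rule.** Standard error = 0.35 × √(2/48) = 0.0714, and 0.21 / 0.0714 = 2.94.

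- One-sided 0.05, as planned: Φ(2.94 - 1.645) = 90.2%.
- Two-sided 95% interval, as 13.3.1.2 is read here: Φ(2.94 - 1.96) = 83.6%.

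The step from 90.2% to 83.6% comes from the significance level and is a separate matter from adjustment.

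**3. A plausible baseline correlation.** The protocol gives none, so this is an assumption. With baseline between 0 and 0.25, its SD is 0.25/√12 = 0.072 if uniform and 0.125 at most. With outcome SD 0.35 and a slope of 1 (assumed), rho = 0.072/0.35 = 0.21, and at most 0.125/0.35 = 0.36. The variance saving, rho², is about 4% and at most 13%.

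**4. Gain from always adjusting.** Adjusted SD = 0.35 × √(1 - rho²). Columns 2 to 4 use the normal formula with 48 per arm and the two-sided 95% rule. The last three come from 20,000 simulated normal trials per rho with a true difference of 0. The simulations use t-based intervals and a single-time-point ANCOVA, and the middle strategy lets that ANCOVA replace the interval when the baseline test is significant.

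| rho | Adjusted SD | 95% half-width | Power, always adjusted (formula) | Simulated: never adjusted | Simulated: only if significant | Simulated: always adjusted |
|---|---|---|---|---|---|---|
| 0 | 0.350 | 0.140 | 83.6% | - | - | - |
| 0.2 | 0.343 | 0.137 | 85.1% | 82.6% | 82.6% | 83.7% |
| 0.36 | 0.327 | 0.131 | 88.3% | 83.0% | 83.5% | 87.3% |
| 0.5 | 0.303 | 0.121 | 92.4% | 82.7% | 83.8% | 91.7% |
| 0.7 | 0.250 | 0.100 | 98.5% | 83.0% | 84.8% | 98.2% |

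The baseline test was significant in 4.6-5.1% of trials, so the conditional rule recovers little of the gain. The trigger would fire more often if any of several baseline variables counted, which the text leaves open.

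**5. Type I error at a true difference of -0.21.** Conditional rule: 0.017-0.026. Always adjusted: 0.023-0.027. The nominal level is 0.025, so neither shows material inflation.

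**6. The follow-on tests.** The mean of 0.38 and SD of 0.48 quoted in 8.4 would put Φ(-0.38/0.48) = 21% of a normal distribution below zero, which a flow rate cannot be. In simulated lognormal and gamma samples of 48 with that mean and SD, a Shapiro-Wilk test rejected normality every time. The Mann-Whitney branch is therefore likely. It gives no mean difference to compare with -0.21, and the t-test as written names no margin either.

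**7. Percentage change in SFR.** A gain of 0.08 mL/min is 0.08/0.02 = +400% from a baseline of 0.02 and 0.08/0.20 = +40% from 0.20. It is undefined from zero.

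**The case against.** The strongest defence is that the decision rule is single and unconditional: the interval against -0.21 comes first, and everything after it can be read as further analysis. On that reading the unadjusted interval is valid, and at the planning level it has 90.2% power without any covariate. The narrow entry range makes baseline a weak predictor, so the gain is modest. All of this stands. What remains is that the ANCOVA sentence does not state its own role, and that precision is lost whenever the correlation is above zero.

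A reader might infer more than the documents support:

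- **That the normality test switches the non-inferiority comparison to Mann-Whitney.** It governs only the further analysis, and the precision loss does not come from that step.
- **That the conditional rule inflates false non-inferiority claims.** The simulation shows no such effect, even when the ANCOVA is allowed to replace the interval.
- **That power would rise to 92-98%.** That needs correlations of 0.5-0.7. Even at the largest possible baseline SD, the slope would have to be 0.5 × 0.35/0.125 = 1.4 to 0.7 × 0.35/0.125 = 1.96.
- **That omitting the strata is an error in itself.** The statistical analysis plan, not shown, may deal with it. Since 9.6 names no strata, the covariate cannot yet be specified. Cause of xerostomia is no ready substitute, because 8.1 lets a patient meet both criteria.
- **That percentage change fails for every outcome.** For VAS, entry requires at least 4, so the ratio is defined.

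**Conclusion.** The point holds as a matter of efficiency and clarity, not of validity. The primary comparison leaves out a baseline measurement taken on everyone and brings it in only on a trigger that is rarely met and incompletely defined. On the range compatible with the entry cap, always adjusting adds roughly 1 to 5 percentage points of power, from about 83-84% to about 84-88%, and narrows the 95% half-width from 0.140 to 0.137-0.131 mL/min.

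These figures assume 48 evaluable per arm, SD 0.35, no true difference, a two-sided 95% interval and a slope of 1. The gain is larger only if the correlation is higher, and the documents do not give it. The percentage-change point is secondary and confined to SFR.

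**What to change.** In 13.3.1.2, and in the matching text of the protocol summary:

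1. State that the single primary analysis is an ANCOVA of week-12 unstimulated SFR on arm and baseline SFR, whatever any baseline test shows. Add the factors used to stratify randomisation once 9.6 names them.
2. State that non-inferiority is concluded if the lower limit of that model's 95% confidence interval for experimental minus control lies above -0.21.
3. Delete the baseline-significance trigger.
4. Label the t-test/Mann-Whitney comparison as supportive only, since neither tests the margin as written.

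In 13.3.2.1, replace mean percentage change in SFR with absolute change adjusted for baseline. The VAS measure need not change on this ground.

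The cost is wording, settled before the outcome data are analysed. Baseline SFR is already collected, and no extra visits or patients are needed. The stratification factors must be named before they can be added.

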## **10.2. Evaluation of efficacy**

### **10.2.1. Salivary flow rate (SFR) test**

- Visit 2 (Week 0) is replaced by screening test.
- Evaluation at Visit 3 (Week 4), Visit 4 (Week 8), Visit 5 (Week 12).

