#### **13.3.2.2. Statistical methods**

- To analyze the secondary outcomes, in the case of continuous outcome measures, a normality test for the distribution of data will be initially performed. In the case of non-normally distributed data, the data will be transformed to a normal distribution using the log-transformation or square root transformation methods.
- The analysis will proceed using either parametric or non-parametric methods. Specifically, an independent T test or Mann-Whitney U test will be performed to compare values between the two groups.
- The Paired T test or Wilcoxon signed-rank test will be performed to compare intragroup continuous values.
- The group and time interaction effect of repeated-measures data will be analyzed through repeated-measures analysis of variance (ANOVA) or ANCOVA, or through the GEE model test based on the nature of the data.
- The level of significance will be set at  $p < 0.05$ .

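### Baseline salivary flow is brought in only after a significant baseline test; prespecify the adjustment for the deciding week-12 comparison instead

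*Protocol*

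**What the plan says.** The primary outcome in section 13.3.1.1 is a single time point: "Unstimulated Salivary Flow Rate (SFR) after 12 weeks of treatment". Section 13.3.1.2 sets the decision rule: "We will calculate the 95% CI of the mean difference in the unstimulated SFR between the two groups after 12 weeks of medication". The lower limit is compared with -0.21, and no covariate is named.

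The next bullet of 13.3.1.2 is introduced as further analysis. It has a normality check, after which "a t-test will be performed to compare the two groups in terms of the primary outcomes; otherwise, the Mann-Whitney U test will be performed". It ends with the conditional rule: "If there is a significant difference in baseline values between the two groups, repeated-measures analysis of covariance (ANCOVA) will be performed". The statistical methods in the protocol summary repeat all of this.

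Section 13.2 plans the baseline comparisons: "To confirm the validity of the random allocation, demographic and baseline values between the experimental and control groups will be compared and evaluated". No level is given for the test that fires the rule. The only general testing level stands in the section on secondary outcomes (13.3.2.2, "The level of significance will be set at" p < 0.05). The baseline variables that count are not listed.

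Section 10.2.1 supplies the data: for baseline, "Visit 2 (Week 0) is replaced by screening test"; on treatment, "Evaluation at Visit 3 (Week 4), Visit 4 (Week 8), Visit 5 (Week 12").

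**The concern.** Three things are unsatisfactory as written.

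- **The trigger.** When allocation is random, any baseline difference is due to chance. A significance test therefore says nothing about whether the variable predicts week-12 flow or how far an imbalance moves the result. A modest imbalance in a strongly prognostic variable matters; a significant one in an irrelevant variable does not.
- **The model that follows.** The limit of -0.21 belongs to a week-12 difference. A repeated-measures model over weeks 4, 8 and 12 can yield several group effects, and the text does not name the week-12 one.
- **The standing of the result.** The text does not say whether the ANCOVA bears on the non-inferiority conclusion or only accompanies it.

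At stake are precision that the trial could have without further data, and protection of the deciding interval against the particular imbalance that this randomisation happens to produce.

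**Working it through.** **Inputs from the protocol.** SD 0.35, margin 0.21, one-sided alpha 0.05, power 90%, 48 evaluable per arm, 60 with 20% dropout (8.4); unstimulated SFR at entry at most 0.25 mL/min (8.1); planning data 0.38 ± 0.48 on pilocarpine 5 mg (8.4).

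**Assumed, because not given.** Two-sided 0.05 for the baseline test; the baseline to week-12 correlation (rho).

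**1. The plan's own figure.** n = 2 × 0.35² × (1.645 + 1.282)² / 0.21² = 47.6, so 48 per arm; 48 / 0.8 = 60. This reproduces.

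**2. How often the trigger fires.** With k independent baseline tests at 0.05, the chance is 1 - 0.95^k: 5% for one, 10% for two, 23% for five, 40% for ten.

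**3. A plausible rho.** rho = slope × SD(baseline) / SD(week 12).
- On a range of 0 to 0.25 the baseline SD cannot exceed 0.25 / 2 = 0.125. If values are uniform it is 0.25 / √12 = 0.072.
- With a slope of 1, rho = 0.072 / 0.35 = 0.21, and at most 0.125 / 0.35 = 0.36.
- For rho 0.5 the slope must be at least 0.5 × 0.35 / 0.125 = 1.4 (2.4 if uniform). For rho 0.7 it must be at least about 2.0 (3.4 if uniform).

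**4. Shift left by a just-non-significant imbalance.** Shift = rho × 0.35 × 1.96 × √(2/48), where √(2/48) = 0.204.

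| rho | shift (mL/min) | share of 0.21 |
|---|---|---|
| 0.21 | 0.029 | 14% |
| 0.36 | 0.050 | 24% |
| 0.5 | 0.070 | 33% |
| 0.7 | 0.098 | 47% |

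**5. Power under the 95% interval rule, true difference 0, 48 per arm.**
- Unadjusted: standard error 0.35 × 0.204 = 0.0714; 0.21 / 0.0714 = 2.94; Φ(2.94 - 1.96) = 84%. This is below 90% because a 95% interval implies one-sided 0.025, while the sample size used 0.05. That is a separate matter.
- Adjusted: the standard error is multiplied by √(1 - rho²). At rho 0.21, Φ(3.00 - 1.96) = 85%. At rho 0.36, Φ(3.15 - 1.96) = 88%. The formula gives 92% and 98% at 0.5 and 0.7.

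**6. Type I error at a true difference of -0.21** (simulation, 40,000 normal trials per setting, 48 per arm).
- Always unadjusted: about 2.5% overall.
- If a triggered ANCOVA replaced the unadjusted interval: 2.4%, 2.2% and 1.8% for rho 0.3, 0.5 and 0.7. There is no inflation.
- Conditionally, at rho 0.3: about 13.5% of trials have a non-significant imbalance of more than 1 standard error favouring the experimental arm. In these the unadjusted interval gives 5.4% false non-inferiority, against 2.5% with ANCOVA. In the mirror-image trials it gives 0.5%, and power at equality is 73% against about 86% with ANCOVA.

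**The case against.** **An unadjusted, prespecified difference is valid.** Its interval keeps nominal coverage over randomisations. This stands. A reader might infer from the conditional rates that the rule inflates false claims of non-inferiority. The simulation does not support that, since favourable and unfavourable imbalances offset each other.

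**The ANCOVA sentence sits under further analysis.** A reader might infer that the deciding analysis switches with the data. The more natural reading is that the week-12 interval decides in every case and is never adjusted. That removes most of the data-dependence charge. What remains is an adjustment that appears only in a minority of trials and whose bearing on the conclusion is unstated.

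**The share of trials left without an ANCOVA.** A figure of 95% holds only for one trigger variable at 0.05. The protocol speaks of baseline values in the plural and gives no level.

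**The larger effects need high correlations.** Shifts of a third to a half of the margin, and power of 92 to 98%, require rho 0.5 to 0.7. Step 3 shows that the entry cap makes these hard to reach without slopes well above 1.

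**Skewed data.** The planning SD of 0.48 exceeds its mean of 0.38 for a quantity that cannot be negative, so gains computed under normality are not assured. This stands and calls for a robust check.

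**Detail may be left to the SAP.** The choice of contrast often is, and the protocol does not say that visits would be averaged. The significance trigger, however, is fixed in the protocol itself.

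**Conclusion.** The point holds as a should-fix and a free improvement, not as an error that invalidates the decision rule. A baseline significance test is a poor trigger for adjustment, and the model it brings in is tied neither to the week-12 difference nor to the decision.

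At 48 per arm, SD 0.35 and rho of about 0.2 to 0.36, the cost is a possible uncorrected shift of 0.03 to 0.05 mL/min and a forgone power gain of about 1 to 4 points. These figures rest on a slope of 1, a baseline range of 0 to 0.25 mL/min, approximate normality and a two-sided 0.05 trigger. Higher correlations would raise them; a correlation near zero would remove them. The objection to the trigger itself does not depend on rho.

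**What to change.** - In 13.3.1.2 and the summary, delete the baseline-significance condition. In 13.2, describe baseline by arm without tests.
- Take the deciding estimate in every case from an ANCOVA of week-12 unstimulated SFR on treatment and screening unstimulated SFR, plus the randomisation stratification factors. Section 9.6 says the blocks are stratified but does not name the factors, so name them. Compare the lower limit of the 95% interval for the adjusted difference (experimental minus control) with -0.21.
- If a repeated-measures model is preferred, name its week-12 contrast as the deciding quantity.
- Keep the unadjusted difference as a sensitivity analysis. Because of the likely skew, check the adjusted interval with robust or bootstrap standard errors.

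The cost is a wording change and a few extra model fits. Screening SFR is already measured, so no patients, visits or measurements are added.
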